#### Secondary outcomes

2.7.2

Exploratory outcome data will be collected at baseline and post-intervention follow-up at 3, 6, and 12 months. These data will include patient dietary intake, patient weight and lean body mass trajectories, patient treatment tolerance, household food and nutrition security, and caregiver burden and distress. A medical record review will be conducted to collect data related to cancer treatment tolerance, including dose/dose modifications, treatment delays, lengths of hospitalizations, and toxicity. Anthropometric data will be collected at each assessment visit including height, weight, BMI z-score (calculated), and mid upper arm circumference. Questionnaires will be sent to the caregivers via REDCap if they are unable to complete them in clinic. Caregiver reported data collected at baseline only will include personal characteristics (medical history, demographic information, time spent caregiving), participation in community and federal food and nutrition assistance programs, meal and meal-time behaviors, and preferences for supportive care. Additionally, caregivers will be asked to share the reasons for joining the study and nutrition challenges they are experiencing.

Food security will be assessed using the two-item *Hunger Vital Signs* screener, which asks caregivers about food availability at home. Responses are reported anchored by the words “Often true”, “Sometimes true”, and “Never true” [26,27]. Household nutrition security and food choice healthfulness will be assessed using adapted survey instruments developed by Calloway and colleagues [28]. The *Nutrition Security* module (4 items) evaluates whether families have consistent access to foods that meet their nutritional needs, while the *Healthfulness of Choice* module (3 items) assesses the quality and healthfulness of food options available and selected within the household. Each instrument contains short questions designed to capture constructs beyond traditional food insecurity, emphasizing nutritional adequacy and choice characteristics. These tools have been shown to be feasible, reliable, and valid for use in community-based studies, and they provide an expanded perspective on how households experience and manage nutritional insecurity. In this study, items and response options were unchanged; only the recall period was shorted to ‘past 3 months.’

Caregiver burden and distress will be assessed using standardized Patient-Reported Outcomes Measurement Information System (PROMIS) instruments. Specifically, caregivers will complete the PROMIS *Satisfaction with Social Roles and Activities* short form and the PROMIS *Emotional Distress - Anxiety* short form. The *Satisfaction with Social Roles and Activities* instrument measures the extent to which individuals are content with their ability to perform usual roles in work, family, and social life, providing insight into the functional impact of caregiving demands. The *Emotional Distress* instrument evaluates symptoms of anxiety and related emotional strain. PROMIS measures have been rigorously validated across diverse populations and use T-scores standardized to the U.S. general population (mean = 50, SD = 10), enabling comparability across studies.

*Patient dietary intake* will be assessed using the Automated Self-Administered 24-h Dietary Recall (ASA24), a free, validated, computer-based tool developed by the National Cancer Institute that provides standardized reporting of total caloric intake, macronutrients, micronutrients, and dietary patterns [29]. Caregivers will complete one 24-h recall on behalf of their child (patient) at each of the assessment time points (baseline, 3, 6, and 12 months). For the first recall for each participant, a trained research staff member will assist participants and will enter data into the ASA24 system on participants’ behalf. After the first recall, caregivers will be encouraged to complete subsequent recalls on their own. However, to reduce burden and support caregivers who require extra support, a research team member will be available to assist caregivers in all subsequent recalls.

### Data analysis plan

2.8

Feasibility and acceptability will be evaluated as the primary outcomes and interpreted relative to predefined progression criteria (Table 2), consistent with published guidance for pilot and feasibility studies [22,23]. Criteria encompass recruitment, retention, assessment completion, intervention adherence, and acceptability and were selected based on prior literature, anticipated caregiver burden, and intervention logistics. Feasibility will be considered established if at least four of the five criteria are met, supporting progression to a future definitive trial.

Descriptive statistics will be selected based on variable type and distribution. Continuous variables will be summarized using means and standard deviations or medians with interquartile ranges, as appropriate, while categorical variables will be described using frequencies and percentages. Acceptability items measured on 5-point Likert scales (1 = strongly disagree to 5 = strongly agree) will be summarized using medians and interquartile ranges, with a median score ≥4.0 indicating acceptable or useful intervention components. Frequencies and percentages will also be presented to enhance interpretability. Distributional assumptions will be assessed through visual inspection.

Secondary endpoints will examine exploratory clinical and behavioral outcomes, including changes in patient dietary intake, weight and lean body mass trajectories, and treatment tolerability. Additional secondary outcomes will include changes in household food and nutrition security and caregiver burden and distress. Given the pilot nature of the study, these outcomes will be analyzed descriptively by comparing pre- and post-intervention measures to inform future hypothesis-driven trials.

### Potential risks and benefits

2.9

This study poses no greater than minimal risk, with anticipated risks comparable to those encountered during routine clinical care. Potential risks include dissatisfaction with meal taste or variety; inadvertent exposure to food allergens or intolerances; transient gastrointestinal symptoms (e.g., bloating, constipation, diarrhea) related to dietary changes; emotional discomfort during nutrition- or caregiving-related discussions; and risks to privacy or confidentiality associated with collection of personal health information. Food preferences, allergies, and intolerances will be assessed at enrollment, and meals will be tailored within the constraints of the meal provider's standard offerings. Meals align with oncology nutrition guidelines, and any nutrition-related concerns or symptoms will be reviewed by the study dietitian. Coaching staff are trained in supportive communication, and participants experiencing emotional distress will be referred to institutional psychosocial support services. Risks related to privacy and confidentiality will be minimized through established data security and confidentiality procedures.

Participants may experience several potential benefits. Children may benefit from access to medically tailored meals designed to support adequate nutrient intake, weight stability, and management of treatment-related side effects. Caregivers may benefit from reduced burden related to meal planning and preparation, improved household nutrition security, and increased knowledge, skills, and confidence in supporting their child's nutrition through individualized coaching. The combined provision of meals and coaching may help reduce caregiver distress and support the development of sustainable, healthy eating practices beyond the intervention period. At a broader level, this study will contribute to understanding the feasibility and potential impact of food-as-medicine interventions in pediatric oncology and may inform future programs to support families during cancer treatment.

### Safety reporting

2.10

Adverse events (AEs) that are unexpected and deemed at least possibly related to study participation will be documented and graded using the Common Terminology Criteria for Adverse Events (CTCAE v5.0). During coaching sessions, caregivers will be asked about concerns related to meals, treatment-related nutrition side effects, or other health events, and unresolved reportable AEs will be followed until resolution. Given the minimal-risk nature of this dietary intervention, unrelated or clearly incidental events will not be recorded. Serious adverse events (SAEs) resulting in death or deemed life-threatening will be reported to the IRB within 48 h of notification; all other related SAEs or unanticipated problems will be reported within 7 days. AE documentation will be maintained in REDCap and reviewed biannually, with summary reporting at continuing review. Early stopping is not anticipated; however, the study may be suspended or terminated in the event of unexpected related SAEs, poor recruitment or retention, or protocol deviations that compromise safety or data integrity. A formal Data and Safety Monitoring Board is not required for this minimal-risk pilot study.

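### The adverse event rule covers only events that are both unexpected and related, so non-serious meal-related harms that the protocol itself anticipates fall outside the adverse event record

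*Protocol article*

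**What the plan says.** Section 2.10 of the protocol article (Safety reporting) sets the entry rule for the adverse event record: "Adverse events (AEs) that are unexpected and deemed at least possibly related to study participation will be documented". Events that enter are graded by CTCAE v5.0, kept in REDCap and reviewed twice a year, with a summary at continuing review. The same section says what stays out: "unrelated or clearly incidental events will not be recorded", and justifies this by the minimal-risk nature of the intervention.

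Serious events have their own sentences. For the gravest, "Serious adverse events (SAEs) resulting in death or deemed life-threatening will be reported to the IRB within 48 h of notification". For the rest, "all other related SAEs or unanticipated problems will be reported within 7 days".

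Section 2.9 (Potential risks and benefits) lists what the investigators foresee from the meals, including "inadvertent exposure to food allergens or intolerances; transient gastrointestinal symptoms (e.g., bloating, constipation, diarrhea) related to dietary changes". It adds that "any nutrition-related concerns or symptoms will be reviewed by the study dietitian".

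On how events come to light, 2.10 says that at coaching sessions "caregivers will be asked about concerns related to meals, treatment-related nutrition side effects, or other health events". Table 1 also schedules adverse event reporting in weeks 1–8, in weeks 9–12 and at 3, 6 and 12 months, and schedules medical record review in every column.

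**The concern.** A harm listed in the protocol as a risk of the intervention is, in ordinary usage, an expected one. If expectedness decides whether an event is recorded at all, and not merely how fast it is reported, then the harms most plausibly caused by the meals are the ones the record leaves out.

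What is at stake is the tolerability information passed to the next trial. The study is meant to inform a definitive randomized trial in children on active cancer treatment. An adverse event summary that contains few or no gastrointestinal or intolerance events could be read as evidence that the meals were well tolerated, when it may only reflect the entry rule.

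**Working it through.** No figure in the plan bears on this point and no formula applies. The check sets the entry rule against the listed risks, and then asks whether any other data source in the article fills the gap.

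**Step 1: classify events under 2.10 as written.**

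| Type of event | Treatment under 2.10 |
|---|---|
| Unexpected, at least possibly related | Documented and graded |
| Expected, at least possibly related, non-serious (for example, diarrhea after the dietary change, or mild intolerance) | Fails the entry rule; not named in the exclusion sentence |
| Related and serious, expected or not (for example, a serious allergic reaction) | Reported to the IRB within 48 h or 7 days |
| Unrelated or clearly incidental, non-serious | Explicitly not recorded |

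The second row is the gap. The inclusion sentence leaves these events out and the exclusion sentence does not mention them, so the two sentences do not fit together.

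**Step 2: look for another route into the adverse event record.**

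- *Coaching sessions (2.10).* Caregivers are asked about meal concerns and other health events. This brings problems to light, but what is then documented is still governed by the entry rule, and only reportable events are followed to resolution.
- *Dietitian review (2.9).* Symptoms are reviewed. Recording and grading are not mentioned.
- *Medical record review (2.7.2).* Toxicity is abstracted as a measure of cancer treatment tolerance, not as harm attributed to the meals.
- *Weekly meal survey (2.7.1).* Reasons for missed meals are collected as adherence data.
- *Acceptability survey (2.7.1).* Common reasons for a child refusing meals are asked as acceptability data.
- *Adverse event row in Table 1.* This schedules reporting but does not change which events qualify.

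Traces of these events may therefore exist in several places. None is stated to be counted or graded as a meal-related harm.

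**Step 3: check the rationale.** The minimal-risk argument in 2.10 is offered for leaving out unrelated or incidental events. It is not offered for leaving out related events that happen to be expected, so widening the entry rule does not conflict with it.

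**The case against.** The strongest reply has four parts.

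1. *'Unexpected' is not defined in the article, and the full protocol may define it.* Section 2.9 speaks of inadvertent exposure and of transient symptoms, so an actual reaction, or severe or persistent symptoms, might count as unexpected. This stands as a limit: some listed events could still enter. It does not rescue ordinary, mild, transient symptoms, which match the risk list exactly.
2. *Limited recording is a deliberate choice for an IRB-approved, minimal-risk study in which safety is not an objective or a progression criterion.* This is true, and it keeps the point away from the primary outcomes. But the stated choice is to omit unrelated events, and the gap concerns related ones.
3. *In a single-arm study of children on chemotherapy, attributing mild gastrointestinal symptoms to the meals is weak.* This is fair. It calls for cautious interpretation of such counts, but does not support having none.
4. *Other sources will show problems.* They may, but not as graded adverse events (see the check above).

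Some stronger readings are tempting, and the document does not support them.

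- A reader might infer that a serious allergic reaction would go unreported. It would not: the serious-event sentences carry no condition that a related event be unexpected.
- A reader might infer from the 75% coaching target that a quarter of families are never asked. The target is a share of scheduled sessions. With 8 weekly sessions and 2 in the taper, 8 + 2 = 10, and 0.75 × 10 = 7.5, so a family that meets the target attends at least 8 sessions and can report an earlier event at the next one.
- A reader might infer that nobody is asked after week 12. Table 1 schedules adverse event reporting at 3, 6 and 12 months, and a condensed article need not describe the procedure.
- A reader might want a confidence limit around a report of zero events. The plan proposes no such interval, and the article gives no event rate from which to judge one.

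**Conclusion.** The point holds for one class of event: non-serious, expected and at least possibly related to the meals. Under 2.10 as written, these are not entered or graded, although 2.9 names them as the foreseeable harms and the exclusion sentence does not mention them. The adverse event summary could therefore understate meal-related harm and overstate how well the meals are tolerated.

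The size cannot be stated as a number, because the article gives no rate for these events and none should be assumed for the purpose. The conclusion rests on two assumptions: that a risk listed in 2.9 counts as expected, and that the full protocol does not define the term otherwise. Recruitment, retention, assessment, adherence and acceptability are unaffected, as is the rule for suspending the study, which refers to serious events. The wording should be corrected, but the defect does not undermine the feasibility decision.

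**What to change.** In 2.10, state that every adverse event at least possibly related to study participation is documented and graded, whether or not it was expected. Keep 'unexpected' only as a trigger for reporting to the IRB. The exclusion sentence can stay as it is, and the two sentences will then agree.

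Optionally, add one item to the weekly caregiver meal survey asking about reactions or gastrointestinal symptoms that the caregiver attributes to the meals. The survey already goes out each week of the intervention, so detection would no longer rest mainly on coaching attendance.

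The cost is a change of wording, one more item on a three-item survey if the option is taken, and somewhat more adverse event entry by study staff. Because gastrointestinal symptoms are common during cancer treatment, the report should present these counts descriptively and say that attribution in a single arm is uncertain.

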## Discussion

3

This protocol describes *From Kitchen to Clinic*, a prospective, single-arm feasibility study evaluating a 12-week, family-centered food-as-medicine intervention for caregivers of children undergoing cancer treatment. The intervention integrates MTM delivery with caregiver coaching, delivered during a critical period following diagnosis when treatment intensity, caregiver burden, and nutrition-related challenges are often greatest. The stepped intervention design - featuring an intensive phase followed by a tapered transition phase - was intentionally selected to balance early support with skill-building and sustainability, while minimizing participant burden.

Despite growing recognition of nutrition as a modifiable contributor to long-term survivorship outcomes, there remains a lack of pragmatic, family-centered nutrition interventions delivered during active pediatric oncology treatment. *From Kitchen to Clinic* addresses this gap by combining MTMs with caregiver coaching to reduce structural and psychosocial barriers to healthy eating. By intervening early, during active treatment rather than survivorship alone, this study aligns with emerging evidence suggesting that dietary patterns, weight trajectories, and cardiometabolic risk may be established during treatment and persist thereafter. This protocol contributes to the limited but growing literature on food-as-medicine approaches in oncology and represents one of the few studies to examine MTMs within a pediatric, family-centered model.

Several challenges are anticipated in the implementation of this study. Recruitment and retention may be affected by the competing demands faced by families during active cancer treatment, including frequent clinic visits, hospitalizations, and caregiving responsibilities. To mitigate these challenges, the study design emphasizes flexibility in scheduling, remote data collection options, and integration with existing clinical workflows. Participant burden related to repeated assessments and dietary recalls may also impact completion rates; therefore, feasibility outcomes related to assessment completion and participant feedback will be closely monitored. Intervention adherence may vary due to treatment-related symptoms, changes in appetite, or evolving family preferences. The inclusion of caregiver coaching and a tapered intervention phase is intended to support engagement while allowing adaptation to individual family circumstances. Findings related to adherence and acceptability will be critical for refining intervention dose, delivery, and support strategies in future trials.

A key strength of this study is its focus on scalability and real-world implementation. The intervention leverages an established community-based MTM provider and integrates RDN coaching in a manner that could be embedded within standard supportive oncology care. By systematically evaluating feasibility metrics and progression criteria, this study will generate actionable data to inform whether and how the intervention could be expanded to additional clinical sites or populations. If feasibility benchmarks are met, findings from this study will inform the design of a future randomized controlled trial to evaluate effectiveness. Additionally, the integration of household-level outcomes, caregiver-reported measures, and implementation-relevant data positions *From Kitchen to Clinic* to contribute to policy-relevant discussions around food-as-medicine models in pediatric oncology and broader supportive care contexts.

Several considerations will be important when designing subsequent evaluations of this intervention. The present study was intentionally designed as a single-arm feasibility study and therefore does not evaluate the feasibility or acceptability of a comparison condition. This is particularly relevant for a MTM intervention because receipt of the intervention is readily apparent and represents a substantial form of material support. In a future randomized trial, participants assigned to a non-meal condition may have different expectations or experience disappointment related to treatment assignment, which could influence engagement, retention, and patient-reported outcomes, particularly psychosocial measures [30,31].

Accordingly, future studies should carefully evaluate both the content of the comparison condition and the overall trial design. Potential comparators could include usual care, enhanced usual care, or an attention-control condition. Participant-preference designs may also warrant consideration given the tangible nature of the intervention [32]. For example, a partially randomized preference trial could allow participants with strong treatment preferences to select a condition while randomizing those without a strong preference, whereas a conventional randomized trial could prospectively assess treatment preference and examine whether preference modifies adherence, retention, or outcomes. Although preference-based approaches may reduce concerns related to disappointment and differential retention, they also introduce potential selection bias and greater complexity in estimating causal intervention effects. These design considerations should be explored as the intervention progresses from feasibility testing to larger-scale effectiveness evaluation.

In summary, *From Kitchen to Clinic* is a novel, family-centered feasibility study designed to address a critical gap in pediatric oncology care by integrating medically tailored meals with caregiver coaching during active treatment. By evaluating feasibility, acceptability, and adherence, and generating preliminary data on dietary, household, and caregiver outcomes, this study will provide essential groundwork for future trials and implementation efforts. Ultimately, this work aims to advance the role of food-as-medicine approaches in pediatric oncology and inform scalable strategies to support children and families during cancer treatment.

## Ethics approval and clinical trial registration

The trial was granted full ethics approval by the Institutional Review Board at CHOP (IRB 26-024340). The trial is registered with ClinicalTrials.gov ID: NCT07454902.

